| Statistical methods (20a,b,c) | Quantitative data entry will be done in IBM’s SPSS version 26. The sub-Country research teams will be responsible for verifying the data and a second verification will be done by the researcher to monitor data quality. Questions about data inconsistencies or missing values will be sent to sites and will be resolved on an ongoing basis. The participant will form the unit of analysis and intra-cluster correlation coefficient will be accounted for. All analysis will be by intention to treat Descriptive statistics will be performed by computing means, standard deviations, and minimum and maximum values for continuous variables, and frequencies and percentages for categorical variables. As part of quality control and descriptive analysis of the data, the distribution of variables to detect outliers will be examined. Descriptive statistics will be tabulated for individual clusters and aggregated across clusters.  On evaluating the effect of socio-cultural beliefs on Postpartum Family Planning uptake among postpartum mothers in Kisumu County, descriptive statistics on of prevalent sociocultural beliefs about PPFP will be summarized into frequencies and percentages. Bivariate analysis of effects of sociocultural beliefs on PPFP uptake will be done and presented on two-by-two (2x2) tables with Chi-square being the inferential statistics where P-value will determine the significance of homogeneity of proportions and odds ratio (OR) and 95% confidence interval (95% CI) will demonstrate the strength of the relationship. Binary logistic regression analysis will be done to adjust for confounders of sociocultural beliefs as determinants of PPFP uptake  Perceived individual control of Postpartum Family Planning choice among postpartum mothers in Kisumu County will be analysed using descriptive statistics aggregated based on sociodemographic aspects and presented in tables with means, median, range and standard deviation. This will further be analysed by student t-test to ascertain the significance in differences in means for the determinants of perceived control of family planning choice Significant determinants will be fitted in multilinear regression analysis to adjust for confounders  Fertility intentions for postpartum mothers will be disaggregated based on sociodemographic aspects and other individual characteristics. Intention to use PPFP will be simplified in proportions of the categorical yes or no to appointment for PPFP. Bivariate analysis of determinants of fertility intentions will be done and presented in two-by-two (2x2) tables with Chi-square being the inferential statistics. Binary logistic regression analysis will be done to adjust for confounders of determinants of fertility intentions.  Likewise, level of intention will be measure by Likert scale and analysed by t-test statistics after normality testing and adjusted for in linear regression analysis.  Postpartum Family Planning uptake between control and intervention groups of will be compared by use of simple clinical superiority in the proportions.  Bivariate analysis with chi-square statistics will be used to analyse the determinants of Postpartum Family Planning uptake between control and intervention groups and thus will form the selection criteria for inclusion in final regression model. Binary logistic regression analysis will be applied to adjust for confounders |

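### The bivariate tests for beliefs, yes/no intention and perceived control are fixed to two-group comparisons, so a continuous or multi-level determinant must be collapsed before testing; for perceived control that test also decides what enters the regression

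*Protocol*

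**What the plan says.** All of this stands in the Protocol, Statistical methods (20a,b,c), which works in two steps.

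- **Sociocultural beliefs and uptake (objective 1).** The bivariate analysis "will be done and presented on two-by-two (2x2) tables with Chi-square being the inferential statistics", with an odds ratio and 95% confidence interval. Then: "Binary logistic regression analysis will be done to adjust for confounders of sociocultural beliefs as determinants of PPFP uptake".
- **Perceived control (objective 2).** The score is described by sociodemographic group and then "analysed by student t-test to ascertain the significance in differences in means for the determinants of perceived control of family planning choice". Next: "Significant determinants will be fitted in multilinear regression analysis to adjust for confounders".
- **Fertility intention as yes/no (objective 3).** "Bivariate analysis of determinants of fertility intentions will be done and presented in two-by-two (2x2) tables with Chi-square being the inferential statistics". Then: "Binary logistic regression analysis will be done to adjust for confounders of determinants of fertility intentions".
- **Intention as a Likert score.** A t-test followed by linear regression. The groups that the t-test compares are not stated.
- **Determinants of uptake (objective 5).** A bivariate chi-square with no 2x2 restriction. Its result decides which determinants enter the final logistic model.

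The determinants are described only as sociodemographic aspects and other individual characteristics. The row that follows says that no further methods are planned.

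**The concern.** A 2x2 table takes a two-level determinant, and a Student t-test compares two groups. Sociodemographic and individual characteristics usually include some that are counts, measurements or several categories. As worded, the named tests accept these only after they have been reduced to two groups.

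Two things are at stake. First, collapsing a graded determinant discards information, so a real association is more easily missed, and the result depends on where the cut falls. Second, where the bivariate result decides entry to the regression, the later model cannot repair the loss, because a determinant that fails the collapsed test is never fitted. The Protocol makes the bivariate result a gate in two places: perceived control, and determinants of uptake under objective 5.

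**Working it through.** **1. Which step forces two groups, and which step gates the model**

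| Analysis | Bivariate test | Two groups forced? | Decides entry to regression? | Regression |
|---|---|---|---|---|
| Beliefs vs uptake (obj. 1) | 2x2 chi-square | Yes | Not stated | Logistic |
| Perceived control (obj. 2) | Student t-test | Yes, for the determinant | Yes | Linear |
| Yes/no intention (obj. 3) | 2x2 chi-square | Yes | Not stated | Logistic |
| Determinants of uptake (obj. 5) | Chi-square | No; r x 2 possible, but a continuous predictor must be grouped | Yes | Logistic |

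Perceived control is the one row where a forced two-group test is also the gate. Under objectives 1 and 3 the two-group form is forced, but no gate is stated. Under objective 5 there is a gate, and the constraint is weaker.

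**2. Size of the loss, as an illustration**

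The Protocol states no figure for this, so there is none to reproduce. The only input from the document is the total of 246 women (Sample size (14)), used for scale. The following are assumptions: the determinant is normally distributed, its effect is linear, observations are independent, and all 246 women contribute.

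A cut at quantile q keeps the fraction φ(z_q)² / [q(1−q)] of the information, where φ is the standard normal density. For a median split, φ(0)² / 0.25 = 0.1592 / 0.25 = 0.637 = 2/π.

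| Cut | Kept | Lost | 246 women act like |
|---|---|---|---|
| 50/50 | 0.637 | 36% | 157 |
| 60/40 | 0.622 | 38% | 153 |
| 70/30 | 0.576 | 42% | 142 |
| 80/20 | 0.490 | 51% | 121 |
| 90/10 | 0.342 | 66% | 84 |

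A determinant that is binary by nature loses 0%.

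For comparison, k equal ordered groups that are scored keep k·Σ[φ(a) − φ(b)]², where a and b are the limits of each group. Three groups lose 21%, four lose 14% and five lose 10%. These values hold for a scored (trend) test. An unordered r x 2 chi-square spends r − 1 degrees of freedom and does not reach them for a linear effect.

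**3. What it means for the perceived-control screen**

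Let r be the correlation between a determinant and the perceived-control score. Power at two-sided 0.05 is approximately Φ(atanh(r)·√(246 − 3) − 1.96). A median split replaces r by r·√(2/π) = 0.798r.

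- r = 0.20, natural units: 0.2027 × 15.59 = 3.16, power 88%. Split: 0.1610 × 15.59 = 2.51, power 71%.
- r = 0.15, natural units: 0.1511 × 15.59 = 2.36, power 65%. Split: 0.1203 × 15.59 = 1.87, power 47%.

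Under these assumptions the chance that such a determinant fails the screen rises from 12% to 29%, and from 35% to 53%. Both values of r are chosen for illustration.

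**The case against.** The strongest reply is that regression follows the bivariate step for every outcome. Logistic and linear models accept determinants in natural units or with several levels, and nothing in the Protocol says they are split there. This stands. A reader might infer that determinants are tested only by two-group methods; the section contradicts that. The reply does not cover perceived control, where the two-group test decides what reaches the model.

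Other limits also stand:

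- **Uptake.** A reader might infer that all determinants of uptake are forced into 2x2 tables. The 2x2 wording covers beliefs only, and objective 5 allows r x 2 tables.
- **Beliefs.** These are to be summarised as frequencies and percentages and may be yes/no items, in which case nothing is lost.
- **Scale scores.** Perceived control and the Likert intention score are outcomes here. They are compared as means and modelled linearly, and are not cut in two.
- **Named variables.** Age, parity and education come to mind, but the section names none of them.
- **Residual confounding.** It would arise if a split variable were used for adjustment. The Protocol does not say that it would be.

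It can also be said that covariate coding and cut-points belong in a statistical analysis plan, which is not at hand. That is fair, and the lack of a cut-point is not counted here. The point is that the Protocol itself names two-group tests as the inferential method.

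**Conclusion.** The point holds in a narrow form. For beliefs against uptake, yes/no intention and perceived control, the stated bivariate tests accept only two-group determinants. For perceived control the consequence is lasting, because a determinant missed after collapsing never enters the regression. For objective 5 the gate exists with a looser test, which still needs a continuous predictor to be grouped.

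The size cannot be read from the Protocol. A reader might take away that about a third of the information is lost throughout; that is the value for a median split of a normal predictor with a linear effect. The range is 0% for a determinant that is already binary, 36% for a median split and 66% for a 90/10 cut, ignoring clustering.

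These are secondary analyses. The comparison of uptake between arms (objective 4) is not affected. This is an inexpensive improvement to the determinant analyses, not a threat to the trial's main result.

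**What to change.** Amend Statistical methods (20a,b,c) as follows:

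1. For beliefs and yes/no intention, replace the 2x2 requirement by r x 2 tables for determinants with several categories.
2. For perceived control, replace the two-group t-test by ANOVA, or by the linear model already planned, so that determinants with more than two levels need no collapsing.
3. Test continuous determinants in natural units in the logistic or linear model. Do this at the screening step too, for perceived control and for objective 5, so that entry to the model does not depend on a cut.
4. If a 2x2 display is wanted, keep it descriptive and fix the cut-point before the data are seen.

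The cost is a change of wording. The data, sample size and software (SPSS) stay the same.

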|  | Choice of comparators  The intervention is Antenatal provision of Postpartum Family Planning (PPFP) Information and appointment setting for 14 weeks postpartum follow-up. This intervention can be feasibly applied to the current Maternal and Child Health services in Kenya  The control comparator for this study is the routine care that is given to antenatal mothers. It was chosen because it is applied uniformly in the setting from which the participants were drawn. Secondly, it is ethically acceptable because the standard care will not be denied from the control group. Third is that it is a relevant comparator as it the actual services that the treatment is being compared to and bears close semblance to the intervention. Lastly, the comparator will control for threats to internal validity. |
| Objectives (7) | The researcher will specifically:   1. Evaluate effect of socio-cultural beliefs on Postpartum Family Planning uptake among postpartum mothers; 2. Assess perceived individual control of Postpartum Family Planning choice among postpartum; 3. Analyse fertility intentions for postpartum mothers after the intervention; 4. Compare Postpartum Family Planning uptake between control and intervention groups of postpartum 5. Examine the determinants of Postpartum Family Planning uptake between control and intervention groups of postpartum mothers in Kisumu County. |

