| Outcomes (12) | Primary Outcome  Nature of Fertility decisions postpartum. Primarily the uptake of immediate postpartum FP being the main outcome. To be measured at or after 14 weeks postpartum. It is a proportion.  Secondary Outcome  1. Fertility intentions. Primarily whether they accept to book an appointment for postpartum family planning. Will be assessed soon after the intervention has been administered. It will be a proportion of those intending to use PPFP versus those who participated.  2. Knowledge of family planning methods. Will be assessed soon after the intervention has been administered or recruitment (for controls). It will be a proportion of level of knowledge on PPFP among participated.  3. Uptake of postnatal services. Will be measured at 14 weeks postpartum and it will be a proportion of utilization of postnatal services among participants.  4. Perceived control of fertility decision. Will be a proportion among participants. To be measured soon after intervention or recruitment (for the controls)  5. Attitude toward PPFP Will be a proportion among participants. To be measured soon after intervention or recruitment (for the controls)  No harm outcomes are premeditated |
| Participant timeline (13) | This being a behavioural intervention, the recruitment and interventions will be done simultaneously.  Client exit interviews will be done immediately or soonest possible time after the intervention  Questionnaire will be administered at or soon after 14 weeks postpartum.  (see annexes 1 and 2)  [figure not shown] |

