| Sample size (14) | The sample size is estimated based on the following assumptions: among women at three months postpartum, KDHS data report 27% of use of any method (modern or traditional) in Kenya while the CPR in the general population is 53% (KNBS, 2015) . These figures allow the assumption of a desired 26% difference between control and the intervention groups (26% increase in adopting a modern contraceptive by three months postpartum). Therefore the sample size was calculated pairwise for two separate RCT for community arm and the control and the facility arm and the control (Fleiss et al., 2004; Freidlin et al., 2008; Kane, 2018; Rosner, 2015). Rosner, 2015 proposed the sample size determination formula for difference in proportions with consideration of type I and II errors and power (Rosner, 2015; Suresh & Chandrashekara, 2012), N1={z_(1-α/2)*√(p ̅*q ̅*(1+1/k) )+z_1-β*√(p1*q1+(p2*q2)/k)}^2/Δ^2  Where q1=1-p1, q2=1-p2, p ̅=(p1+kp2)/(1+K) , p1, p2 = proportion (incidence) of groups #1 (27%) and #2 (53%) , Δ = |p2-p1| = absolute difference between two proportions (0.26), n1 = sample size for group #1, n2 = sample size for group #2, α = probability of type I error (is set at 0.05), β = probability of type II error (is set at 0.1 i.e. 90% power), z = critical Z value for a given α or β(1.96) and K = ratio of sample size for group #2 to group #1(1). Thus for practical equal sample distribution, the actual sample size shall be 246. Each facility shall have 41 clients |

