| There are no additional methods proposed in this protocols. Any amendments will be communicated. |
| Intention to treat will be applied to protocol non-adherence.  Automatic linear model regression multiple imputation with 5 iterations with history for comparison of variance will be applied in handling of missing values. |
| **Methods: Monitoring** | |
| Data monitoring (21a,b) | Data management team will comprise the PI, Data Clerks at the sites and the study nurse and Community Health Worker: set acceptance rate proportion (those who accepted to participate versus those sampled), monitoring retention (percentage of participants proceeding from recruitment, treatment to follow-up including missing outcome data), monthly forecast of recruitment for the trial period remaining, monitoring loss to follow-up as a proportion of the ones not yet reached by 16 weeks postpartum follow-up to those who were recruited, overseeing data management metrics i.e. rate of electronic data capture, return dates and rate of returns, number of completed follow-up, withdrawal rate, monitoring intervention fidelity by the study nurse or Community Health Worker (CHW), Data quality checks, results dashboard review |
| The interim analysis will be for monitoring purposes from the Kobo toolbox dashboard. It will be used to determine acceptance rate and retention rate and forecasting trial period remaining and the proportion of the unreached or dropout rate. This being a behavioural intervention study, the researcher did not envisage a circumstance warranting prior termination of the trial due to internal factors. |
| Harms (22) | The study doesn’t envisage adverse events as it is a behavioural interventional study seeking to augment a vital preventive service. |
| Auditing (23) | The trial will be audited on monthly basis. The core and site trial team plus the facility in-charge and Sub-county RH coordinator will be involved in the auditing. |
| Ethics and dissemination | |
| Research ethics approval (24) | The study has undergone ethics review by Masinde Muliro University of Science and Technology (MMUST), (MMUST/IERC/013/2021) and has been licensed by the National Commission for Science, Technology and Innovation (NACOSTI), Ref. No. 522628. Informed consent will be sought before participant can be recruited |

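### The t-test screen for perceived control can drop mutually masking determinants before the regression meant to adjust for confounders; prespecify the covariates instead

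*Protocol*

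**What the plan says.** Perceived control is specific objective 2 (Objectives, item 7) and the fourth secondary outcome (Outcomes, item 12), measured soon after the intervention or, for controls, at recruitment.

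Statistical methods (20a,b,c) analyses it in two steps after description. The first is a "student t-test to ascertain the significance in differences in means for the determinants of perceived control of family planning choice". The second is: "Significant determinants will be fitted in multilinear regression analysis to adjust for confounders".

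For the determinants of uptake (objective 5), the same section says that bivariate chi-square results "thus will form the selection criteria for inclusion in final regression model".

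The protocol lists no covariate to be kept whatever its p-value and gives no threshold for the screen. The row after the statistical methods adds: "There are no additional methods proposed in this protocols".

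**The concern.** The regression has a stated purpose, adjustment for confounding, and the entry rule works against it. A confounder is defined by its relation to both the determinant of interest and the outcome. A significant crude difference is neither necessary nor sufficient for that. When two positively related traits act in opposite directions, each crude difference is pulled towards zero by the other. Both can then fail the t-test, although a joint model would show both.

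Two things are at stake for this secondary outcome. Real determinants may go unreported, and coefficients presented as adjusted may lack the variable they most needed adjusting for.

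**Working it through.** **Inputs from the protocol.** Total sample 246 (Sample size, item 14): 6 sites × 41 = 246. Type I error 0.05, which is stated for the sample size only and is borrowed here as the screening threshold.

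**Assumed inputs, because the protocol gives none.** 8, 12 or 16 candidate determinants, all balanced and binary. Two have real effects of +0.4 and -0.4 SD and come from a bivariate normal with latent correlation 0.6 or 0.7; the rest are null. Residual SD is 1 and women are treated as independent.

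**Step 1: masking by formula.** For traits split at the median, the binary correlation is φ = (2/π)·arcsin(ρ), which is 0.410 at ρ = 0.6 and 0.494 at ρ = 0.7.
- Crude difference for the first trait: 0.4 × (1 − φ) = 0.236 and 0.203, so 41% and 49% of the effect is hidden.
- Crude standard error: (2/√246) × √(1 + 0.04(1 − φ²)) = 0.130 and 0.129.
- Chance of passing the screen: Φ(0.236/0.130 − 1.96) ≈ 45% and Φ(0.203/0.129 − 1.96) ≈ 35%.
- Both traits entered: standard error (2/√246)/√(1 − φ²) = 0.140 and 0.147. Detection is Φ(0.4/0.140 − 1.96) ≈ 82% and Φ(0.4/0.147 − 1.96) ≈ 78%.

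**Step 2: simulation with 8 to 16 candidates.**

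| Setting | With the screen | All entered together |
|---|---|---|
| Opposite effects, correlation 0.6 | kept in 42–45% | detected in 78–80% |
| Opposite effects, correlation 0.7 | kept in 33–34% | detected in 74–77% |
| No masking, 0.4 SD effect | detected in 84–86% | detected in 85–87% |

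In the first two rows, being kept is an upper limit on being reported, so the comparison favours the screen. Repeat runs move the figures by up to about three points.

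**Step 3: bias when the confounder is dropped.** Take a determinant with a true effect of 0.50 SD, and a confounder whose crude difference is exactly zero. Let d be the difference in the determinant's prevalence between confounder levels. The confounder's own effect is then −0.50d, and it fails a 5% screen about 95% of the time. The unadjusted estimate is 0.50 × (1 − d²): 0.455 at d = 0.3 and 0.32 at d = 0.6. With the confounder always in the model, 0.50 is recovered.

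**Step 4: false positives.** With K independent null candidates, the chance that at least one is significant is 1 − 0.95^K: 33.7%, 46.0% and 56.0% for K = 8, 12 and 16. In simulation, screening and then regressing gives 34%, 46% and 56%. A full model with no screen gives 34%, 48% and 53%. The screen makes no material difference here.

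**The case against.** **Exclusion is inferred.** The text does not say that non-significant variables are left out, and it gives no threshold. This stands as a limit. Still, naming the significant determinants as those to be fitted serves no purpose if the others enter too, and nothing elsewhere in the protocol keeps any variable in. A later analysis plan could name covariates, but it would have to depart from a rule the protocol already states.

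**The masking case is unfavourable by design.** Equal and opposite effects with correlation 0.6–0.7 are near the worst case. This also stands: the figures show what can happen, not what is expected. The counterweight is that entering everything costs almost no power where there is no masking.

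**A reader might infer that the screen manufactures chance findings and then confirms them.** It is true that most null variables passing the screen stay significant in the regression, because the same data are used twice. But Step 4 shows the same overall error rate without the screen, so the cause is uncorrected multiple testing. Deleting the screen will not cure it.

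**Multiplicity correction is not free.** Holm over the full model lowers detection in the masked case (correlation 0.6) to 43–53%, most or all of the gain. It lowers detection of an unmasked 0.4 SD effect from about 84–86% to 55–66%. It should not be a required part of the remedy.

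**The objective is secondary.** This is correct, and it limits the weight of the point.

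**Conclusion.** The point holds, with moderate weight. The stated entry rule can defeat the regression's stated purpose. Under the assumed masking, it keeps a real determinant in roughly a third to under a half of trials, where joint entry detects it in about three quarters or more. Without masking there is little to choose between the two.

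The direction follows from the rule itself. The sizes rest on an assumed number of candidates, assumed correlations and effects, a 5% screen and independent women. They were worked out for the linear model and not for the logistic model of objective 5.

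A reader might also take this as a flaw in the trial's main result. The documents do not support that: the comparison of uptake between arms is described separately, as a comparison of proportions, and does not depend on this screen.

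**What to change.** In Statistical methods, for objective 2:
- Delete the significance screen and keep the t-tests as description.
- List the pre-intervention sociodemographic determinants in advance. Enter them together, whatever their t-test result, with arm and urban or rural area. Site may replace arm and area if the arm coefficient is not needed, since each site belongs to one arm.
- Report every coefficient with its 95% CI.
- Label the determinant results exploratory. Holm may be added if the team accepts the loss of power shown above.

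Make the same change to the chi-square screen for objective 5, with a shorter list. If both intervention arms reached the planning rate, uptake would be about 0.27 × 82 + 0.53 × 164 ≈ 109 women, or about 7 per term with 16 terms. The linear model has 246/16 ≈ 15 women per term.

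The cost is a wording change with no new data. The downside is slightly wider intervals.

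### The stated imputation rule is a linear model for all missing values, which does not fit the yes/no outcomes analysed by 2x2 tables and binary logistic regression

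*Protocol*

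**What the plan says.** The protocol's rule for missing data, at the end of Statistical methods (20a,b,c), is one sentence: "Automatic linear model regression multiple imputation with 5 iterations with history for comparison of variance will be applied in handling of missing values". It names no variables, no exceptions and no predictors.

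The primary outcome is yes/no for each woman and is summarised as a proportion. Outcomes (12) reads: "Primarily the uptake of immediate postpartum FP being the main outcome. To be measured at or after 14 weeks postpartum. It is a proportion". The first secondary outcome, acceptance of a postpartum appointment, is reduced to yes or no under Statistical methods.

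The same section analyses determinants of both outcomes by chi-square, then by a logistic model. For uptake it says: "Binary logistic regression analysis will be applied to adjust for confounders". The between-arm comparison of uptake is a separate, simple comparison of proportions. On clustering it says: "The participant will form the unit of analysis and intra-cluster correlation coefficient will be accounted for".

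Missing outcomes are foreseen. Data monitoring (21a,b) includes "monitoring retention (percentage of participants proceeding from recruitment, treatment to follow-up including missing outcome data". No expected rate is given.

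**The concern.** A linear regression imputation model draws each missing value from a continuous distribution. For a 0/1 variable it returns values such as -0.2, 0.4 or 1.3. A 2x2 table or a binary logistic model needs two categories, so the imputed data do not fit the analyses that the same section prescribes. The analyst would have to round at some cut-off, drop the imputed values or change the model. Each of these choices would be made after the data are in, and the protocol settles none of them.

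Two features of the sentence add to this. It gives a number of iterations, which is a setting of the algorithm, but not the number of completed data sets to be combined. It also names no predictors, so it does not secure the one predictor that matters most for the arm comparison, the arm itself.

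**Working it through.** **Inputs.** Sample size (14) gives "proportion (incidence) of groups #1 (27%) and #2 (53"%, that is p1 = 0.27, p2 = 0.53 and a difference of 0.26. The total is 246 = 6 sites x 41 = 3 arms x 82. The printed formula gives 72.5, so 73 per arm; a continuity correction gives 80.02, so 81, close to the stated 82. Nothing below depends on that gap; 82 per arm only sets the size of the simulations. Missing rates of 10, 20 and 30% and an intra-cluster correlation (ICC) of 0 or 0.05 are assumptions, because the protocol gives neither.

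**1. Values outside 0 to 1.** A linear model with arm as predictor draws from a normal distribution with mean p and SD = sqrt(p(1-p)), if each arm has its own variance.

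| p | SD | P(below 0) | P(above 1) | Total |
|---|---|---|---|---|
| 0.27 | 0.444 | 0.272 | 0.050 | 0.322 |
| 0.53 | 0.499 | 0.144 | 0.173 | 0.317 |

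An ordinary linear model has one pooled SD, sqrt((0.1971 + 0.2491)/2) = 0.472. The totals are then 0.345 and 0.291, with a mean of 0.318. Simulation with arm as the only predictor gave 32.5 to 32.8% at 10 and 20% missing. Draws from a continuous distribution essentially never equal 0 or 1.

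**2. Crude difference, unrounded, arm in the model.** The mean of the imputed values in each arm is that arm's observed proportion, so the expected difference stays at 0.26 when data are missing completely at random. Simulation (82 per arm, 5 imputations) gave 25.8 to 26.2 points at 10 and 20% missing, across ICC 0 and 0.05.

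**3. Crude difference if the analyst rounds at 0.5.** The share of draws above 0.5 replaces p among imputed women.

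- Separate SDs: 0.302 and 0.524, a difference of 0.222. Overall, 0.26(1-m) + 0.222m gives 25.6, 25.2 and 24.9 points at m = 10, 20 and 30%.
- Pooled SD: 0.313 and 0.525, a difference of 0.212. Overall, 25.5, 25.0 and 24.6 points.

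The loss is therefore 0.4 to 1.4 points of the 26.

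**4. Crude difference if arm is left out of the imputation model.** Imputed women then have the same mean in both arms and contribute no difference: 0.26(1-m) = 23.4, 20.8 and 18.2 points at m = 10, 20 and 30%. This is larger than any rounding effect.

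**5. Between-site variation.** The simulation compared the squared difference between the two sites of an arm after imputation with its full-data value (arm in the model, unrounded).

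| Assumed ICC | Site term | 10% missing | 20% missing |
|---|---|---|---|
| 0 | none | 1.02 | 1.01 |
| 0.05 | none | 0.87 | 0.75 |
| 0 | fixed | 1.24 | 1.48 |
| 0.05 | fixed | 1.06 | 1.17 |

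Without a site term, variation shrinks only if there is real correlation within sites. Fixed site effects err in the other direction.

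**The case against.** The best defence has four parts.

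- **The wording may describe software settings.** The protocol names SPSS 26, and the word automatic could mean that the program picks a model by variable type. The document does not say so, and the model it names is linear. If that was the intention, one clarifying sentence would settle the matter.
- **The main comparison survives.** Uptake between arms is compared as simple proportions, and averaging unrounded linear draws gives a sound difference under step 2. This stands. The incompatibility is confined to the 2x2 tables and logistic models.
- **The rounding bias is not the protocol's.** Rounding is not mentioned anywhere. This also stands: the 0.4 to 1.4 points show the cost of one likely workaround, not of a stated rule.
- **Predictors and the number of data sets are normally left to the statistical analysis plan.** This is fair, and their absence alone would not be a finding. They are raised here because the sentence has to be rewritten anyway.

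A reader might also infer that the plan ignores clustering when it imputes, so that confidence intervals will be too narrow. The document does not support that. The sentence lists no predictors, so it neither includes nor excludes site; the same section commits to accounting for the ICC; and the effect in step 5 disappears at ICC 0.

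**Conclusion.** The point holds as a mismatch between a stated imputation rule and the stated analyses. As written, about 32% of imputed uptake values would be impossible and practically none would be usable in a 2x2 table or a binary logistic regression. This rests on reading the rule literally and on the unqualified reference to missing values, since the sentence does not name the primary outcome.

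It would go too far to conclude that the trial's arm difference will be materially biased. With arm in the model and data missing completely at random, the crude difference stays near 26 points, and rounding would remove at most about 1.4 points at an assumed 30% missing. Leaving arm out would matter more (about 23, 21 and 18 points at 10, 20 and 30% missing), but the protocol does not say that arm is left out. The change is worth making because it is specific and nearly free, not because the expected damage is large.

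**What to change.** Replace the sentence with one that states:

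- Binary variables, including uptake and appointment acceptance, are imputed by logistic regression within a fully conditional specification, and continuous variables by linear regression.
- Study arm is a predictor in the imputation model.
- The imputation is consistent with the commitment to account for the ICC, for example through a random site effect. Study setting (9) and Implementation (16c) give each arm its own sites, so arm is a sum of site indicators and the two cannot both be fixed effects. With only six sites the site variance will be poorly estimated, so the choice deserves thought.
- The number of imputed data sets is given separately from the number of iterations.

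The cost is a wording change and a different option in the software, with no new data. Whether the named package can fit a random site effect in the imputation should be checked before it is promised.
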